# The LIFT trial: study protocol for a double-blind, randomised, placebo-controlled trial of K^+^-binder Lokelma for maximisation of RAAS inhibition in CKD patients with heart failure

**DOI:** 10.1186/s12882-021-02439-2

**Published:** 2021-07-06

**Keywords:** Chronic kidney disease, Heart failure, RAAS, Potassium binder, Randomised

## Abstract

**Background:**

CKD is common in heart failure (HF) and associated with morbidity and mortality, yet life-prolonging medications such as renin-angiotensin-aldosterone inhibitors (RAASi) are underused due to risk of hyperkalaemia. Sodium zirconium cyclosilicate (SZC) is a potassium-binding medication that has been shown to reduce incidence of hyperkalaemia in CKD, non-CKD, and HF populations, which we propose will support maximisation of RAASi therapy.

**Methods:**

We propose a 1:1 randomised, double-blind, placebo-controlled trial in which participants will receive either SZC or placebo. We will up-titrate participants’ RAASi therapy while monitoring their serum potassium levels and adjusting their SZC dose if necessary. Participants with CKD and HF will be recruited from CKD and HF clinics at St George’s Hospital. The total study period will be 18 months; 130 participants will be enrolled for approximately two months each following screening. Our primary outcome will be the proportion of participants who achieve maximum RAASi dose while maintaining normokalaemia. Secondary outcomes include participants reaching maximum RAASi dose without severe hyperkalaemia; time from randomisation to hyperkalaemia; time from randomisation to severe hyperkalaemia; number of RAASi dose escalations per participant; final doses of RAASi therapy; changes in quality of life score, eGFR, ACR, serum sodium, troponin T; number and duration of hospital admissions; and within-participant change in serum potassium compared to baseline.

**Discussion:**

This trial will be the first to examine the use of SZC for the maximisation of RAASi dosing in patients with advanced CKD and HF. We will assess the impact of achieving target RAASi dosing on hospital admission rates and duration of stay, with the hope that optimum RAASi treatment will translate into reduced morbidity and improved QoL. If clinical benefit is demonstrated, we hope that the joint multidisciplinary CKD-HF approach will be expanded.

**Trial registration:**

EudraCT number 2020–002946-18. Registered on 08 June 2020. Online record pending.

## Background

Chronic kidney disease (CKD) is a common comorbidity in individuals with heart failure (HF), with a prevalence of 32% according to a 2013 meta-analysis of over one million individuals [1]. Patients with combined CKD-HF are at 2.3 times greater risk of all-cause mortality than those with HF alone [1]. Potentially life-saving medications for systolic HF are underused in combined CKD-HF due to risk of hyperkalaemia [2]. These medications include renin-angiotensin-aldosterone system inhibitors (RAASi): angiotensin converting enzyme inhibitors (ACEi), angiotensin receptor blockers (ARB), and mineralocorticoid receptor antagonists (MRA) [3, 4].

While numerous national and international guidelines recommend RAASi treatment in patients with combined CKF-HF [5–8], the risk of hyperkalaemia in CKD stage 4/5 patients is high and potentially fatal [9]. There is therefore reluctance amongst general practitioners, general physicians, and cardiologists managing these patients to prescribe medications that may increase serum potassium levels [10].

In a study of 1056 acute heart failure admissions in 851 patients at St George’s Hospital, London, patients with CKD stage 4/5 and systolic HF were less likely to receive ACEi or ARB compared to non-CKD patients (36% vs 84%, *p* < 0.001) and less likely to receive MRA (17% vs 57%, *p* < 0.001) [11]. These findings have led to the establishment of a joint kidney failure-heart failure service at St George’s Hospital, funded by three local clinical commissioning groups, to improve care for these patients. Audit of all new referrals to the kidney failure-heart failure clinic between March and September 2017 showed that only 3% of all patients with left ventricular systolic dysfunction were on maximum-dose ACEi/ARB, and only 2% were on maximum-dose MRA [12].

Recent studies have shown that sodium zirconium cyclosilicate (SZC) can lower serum potassium concentrations in non-CKD, CKD, and HF populations [13–16]. SZC is a zirconium silicate compound that acts as a selective potassium ion trap and is not absorbed from the gastrointestinal tract [17]. In a phase three randomised controlled trial of 258 patients with hyperkalaemia, SZC lowered serum potassium from 5.6 to 4.5 mmol/L in 48 h and maintained serum potassium of < 5.1 mmol/L in 90% of patients (compared with 48% of patients on placebo, *p* < 0.001) [15].

Most studies of potassium binders have been short and none have investigated exclusively the high-risk group of patients with advanced CKD-HF, particularly with an aim to maximise RAASi therapy. Furthermore, this study will augment the currently-limited safety and efficacy data on RAASi maximisation in advanced CKD patients.

The St George’s experience suggests the need for a trial and subsequent clinical implementation of RAASi maximisation in patients with combined CKD-HF. There are significant numbers of patients in our own clinics who may benefit from recruitment into a trial of RAASi maximisation. We therefore propose a 1:1 randomised, double-blind, placebo-controlled trial to investigate the potential benefits of SZC in patients with CKD and HF on maximisation of RAASi therapy.

## Methods & design

### Study setting

Participants will be recruited from the joint kidney failure-heart failure clinic and from other heart failure clinics at St George’s Hospital. Patients discharged from the heart failure wards and inpatients admitted with acute heart failure and referred to the heart failure team will also be approached to take part. The study is being conducted in conjunction with St George’s, University of London and has been approved by the Cambridge NHS Research Ethics Committee [281626], NIHR portfolio [CPMS 47057] and the Medicines and Health Regulator Authority [CTA 12853/0009/001-0001].

### Eligibility criteria

#### Inclusion criteria

For inclusion in the study patients must fulfil all of the following criteria:
Age > 18 yearsHeart failure, clinical or echo confirmed (HFrEF i.e. ejection fraction < 40%); patients with atrial fibrillation will be included provided the EF can be determinedNew York Heart Association class II to IVMost recent serum potassium 5.0–5.5 mmol/LAdequate blood pressure (BP) (> 90 mmHg systolic and without postural hypotension; drop of systolic blood pressure (SBP) > 20 mmHg or feeling dizzy with change in posture; exclude patients with symptomatic hypotension due to high doses of ACEi/ARB or MRA unless the clinical condition has improved)Formal diagnosis of CKD (i.e. two measurements of eGFR < 60 mL/min/1.73 m^2^ taken ≥3 months apart) with stable eGFR < 60 mL/min/1.73m^2^. eGFR to be calculated according to the CKD-Epi formula [18], measured at a single time-point.None or submaximal dose of ACEi/ARB and/or MRA.

#### Exclusion criteria

Patients should not enter the study if any of the following exclusion criteria are fulfilled:

Pregnancy: individuals of childbearing potential must have a negative pregnancy test within 7 days prior to treatment initiation and agree to use highly-effective contraception for the trial period
Active malignancy or infectionBMI > 35 kg/m^2^Poorly controlled blood sugar (HbA1c > 70 mmol/mmol)Recent Acute Coronary Syndrome (ACS) i.e. within three monthsOngoing potassium therapyProlonged QT >  550 ms, congenital QT syndrome and history of prolonged QT requiring drug discontinuationCurrently breastfeedingAllergies to excipients of investigational medicinal product (IMP) or placeboInability to consent

### Recruitment

Participants will be identified by the research team from the clinics mentioned above by consulting clinic lists and patients’ blood test results. Potential participants nearing discharged from hospital will be referred to the research team for participation, provided they are stable and would benefit from RAASi maximisation. Eligibility for the study in all cases will be confirmed by the Principal Investigator (PI) or another study doctor. All patients who fit the eligibility criteria for the study will be approached. At this initial contact, potential participants will be informed of the nature and objectives of the study and any potential risks of participation. If participants agree to take part, they will be invited for screening.

At screening, all participants will have their last three months’ blood tests results for potassium and creatinine reviewed. An electrocardiogram (ECG) will be performed to record participants’ QT interval and further blood samples will be taken for analysis (see *Study Timeline* below). These tests may be done as part of standard care if clinically necessary. Participants of childbearing potential will be required to take a urine pregnancy test. Eligible participants will be asked to complete an E5-QD quality-of-life (QoL) questionnaire and will receive educational material on low sodium / low potassium diets. Again, the PI or study doctor will confirm eligibility in all cases.

Full informed consent will be obtained prior to a participant undergoing any study activities. All potential participants will undergo assessment of capacity, with the opportunity for potential participants to ask questions and have a period of at least 24 h to consider if they would like to take part. The study team will assess if the participant is able to:
Understand the purpose and nature of the research;Understand what the research involves, its benefits, risks and burdens;Understand the alternatives to taking part;Retain the information long enough to make an effective decision;Be able to make a free choice;Be capable of making this particular decision at the time it needs to be made (though their capacity may fluctuate, and they may be capable of making some decisions but not others depending on their complexity).

If the above criteria are met, written consent may be taken by the PI or study doctor. All participants may refuse or discontinue involvement at any time without giving a reason for doing so.

### Randomisation

Participants will be randomised 1:1 to either the placebo or active (SZC) arm of the trial. Randomisation is stratified by patients’ baseline RAASi dose at the start of the trial (individuals on < 50% standard dose vs those on ≥50% standard dose) to ensure equal proportions of RAASi therapies in each group.

We will use the REDCap Randomisation Module (https://wiki.uiowa.edu/display/REDCapDocs/REDCap+Randomization+Module). This module can be turned on by selecting the “Enable the randomization module” checkbox during project creation or after. This would preserve the randomisation procedure independent of the study statistician.

Randomisation will be implemented by the research pharmacy at St George’s. Randomisation codes will be generated by the study statistician on an external spreadsheet. The research pharmacy will be informed by the study team as soon the patient is consented, and will use the randomisation list to assign the participant to their allocated arm. In the case of an adverse event or patient safety issue, emergency unblinding will be performed by the on-call research pharmacist.

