**Fig. 1 Fig1:**
[figure not shown]
Study flow chart. Flow chart demonstrating design of the study. ACEi = ACE inhibitor, ARB = angiotensin receptor blocker, eGFR = estimated glomerular filtration rate, HFrEF = heart failure with reduced ejection fraction, MRA = mineralocorticoid receptor antagonist, OD = once daily, QOL = quality of life, SBP = systolic blood pressure, TDS = three times daily

At initial visit, participants will be initiated on placebo or SZC at initiation dose (i.e. 10 g three times daily). If participants are already taking RAASi medication, they will continue their current medication. If not, the study doctor will start them on appropriate RAASi therapy per local guidance. Participants will be reviewed at 48 h where they will have serum potassium concentration measured and enter the maintenance phase. If serum potassium is 3.5–5.0 mmol/L, participants will begin standard maintenance-dose SZC (i.e. 5 g once daily). For other serum potassium concentrations, and for the remainder of the maintenance phase, dosing will be titrated as outlined in Table 2. If participants experience other adverse effects from RAASi therapy (e.g. symptomatic hypotension, < 90 mmHg recorded systolic blood pressure, postural hypotension), their RAASi dose will be down-titrated if clinically indicated.

**Table 2 Tab2:** IMP dosage protocol

SZC dose at start of visit	Serum potassium at visit	Dose change at end of visit
On 10 g daily	5.0–6.0 mmol/L	Continue 10 g daily
	3.5–5.0 mmol/L	Change to 5 g daily
	< 3.5 mmol/L	Stop
	> 6.0 mmol/L	Stop and initiate rescue
On 5 g daily	> 5.0 mmol/L	Change to 10 g daily
	3.5–5.0 mmol/L	Continue 5 g daily
	< 3.5 mmol/L	Stop
On 0 g daily (i.e. temporary stop)	≤ 5.0 mmol/L	Continue with no IMP
	> 5.0 mmol/L	Initiate 5 g daily

Table 2—Dosage protocol for study visits based on serum potassium measurements. IMP may be restarted two weeks after discontinuation due to hypokalaemia depending on serum potassium result

After screening, recruitment, and randomisation, visits will take place every two weeks (± two days) until the end of the study. The number of visits will depend on participants’ baseline dose of ACEi / ARB / MRA. Patients with no prescribed RAASi at baseline will have seven visits, and others will have six visits.

Following the final study visit, there will be no further follow up visits related to the trial.

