**ARNI**			
Valsartan + sacubitril	24 / 26 mg BD	49 / 51 mg BD	97 / 103 mg BD

Table 3—ARNI = angiotensin receptor-neprilysin inhibitor, BD = twice daily, OD = once daily. For analysis and dose titration, participants’ RAASi doses will be classified as low / medium / maximum based on the values in this table. Note—this is not a dose conversion table

**Table 4 Tab4:** Primary and secondary study outcomes

Objectives	Outcome measures	Timepoints of evaluation
**Primary Objective:** To compare SZC vs placebo with respect to:	Enabling participants to achieve target RAASi dose while keeping serum potassium < 5.6 mmol/L.	Blood test for potassium and RAASi dose
**Secondary Objectives:** To compare SZC vs placebo with respect to:	Achieving maximum dose of MRA and ACEi/ARB with serum potassium < 5.6 mmol/L Achieving maximum dose of MRA and ACEi/ARB with serum potasssium < 6.0 mmol/L Time since randomisation to first occurrence of hyperkalaemia (serum potassium ≥5.6 mmol/L) Time since randomisation to severe hyperkalaemia (serum potassium ≥6.0 mmol/L) Number of ACEi/ARB, MRA dose changes Number and durationof hospital admissions during the study Change in serum potassium at respective visits vs baseline	Blood test for potassium and RAASi dose ever two weeks. Other parameters checked at baseline and end of study.
**Tertiary Objectives:**	None	

Table 4—Primary and secondary study outcomes

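### The single dose cut used for stratification cannot ensure equal proportions of RAASi therapies in the two arms, because it leaves drug class and any-versus-no therapy unbalanced

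*Protocol article*

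**What the plan says.** The protocol article, Randomisation, has one stratification factor: "Randomisation is stratified by patients’ baseline RAASi dose at the start of the trial". The cut and its purpose follow: "individuals on < 50% standard dose vs those on ≥50% standard dose) to ensure equal proportions of RAASi therapies in each group".

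Three other places bear on this:

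- Inclusion criteria admit participants with "None or submaximal dose of ACEi/ARB and/or MRA", so a participant may enter on no RAASi, on one class or on two.
- Study timeline treats untreated participants differently. RAASi is started at the initial visit ("If not, the study doctor will start them on appropriate RAASi therapy per local guidance"), and the visit count differs: "Patients with no prescribed RAASi at baseline will have seven visits, and others will have six visits".
- Outcomes, Table 3, gives a minimum, a half-maximum and a maximum dose per drug. Its footnote says that, for analysis and titration, "participants’ RAASi doses will be classified as low / medium / maximum based on the values in this table", and adds that the table is not for dose conversion. The term used for the reference dose in the Randomisation section does not occur in Table 3 or elsewhere in the article.

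**The concern.** The article gives the design a property: equal proportions of RAASi therapies between arms. Stratification balances only the variable that defines the strata. Within the lower stratum sit untreated participants, low-dose ACEi/ARB users, low-dose MRA users and low-dose users of both. Within the upper stratum, class is equally free to vary. Nothing in the factor holds these groups level between arms.

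This matters because baseline class and dose fix how far a participant has to be titrated to reach the maximum, so they plausibly predict the primary responder outcome. The first secondary responder outcome requires the maximum of both MRA and ACEi/ARB. The article also names the degree of MRA and ACEi/ARB treatment at baseline as a possible subgroup definition. The primary analysis it describes is a χ² test with no baseline adjustment, so a chance imbalance in class would pass straight into the estimated difference.

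**Working it through.** **Trial size.** With response 0.5 versus 0.8, two-sided α = 0.05, 90% power and pooled variance:

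n = [1.96·√(2·0.65·0.35) + 1.2816·√(0.25 + 0.16)]² / 0.3² = (1.322 + 0.821)² / 0.09 ≈ 51.0, rounded up to 52 per arm.

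Power at 52 is 90.6%, and 104 / 0.8 = 130. The plan's figures reproduce. I take 130 as the total, as in the Abstract, so 65 per arm.

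**Chance imbalance in MRA use if nothing balances it.** The article's Background gives MRA use of 17% in CKD stage 4/5 and 57% in non-CKD patients; I use these as a range. The standard deviation of the arm difference is √(2p(1−p)/65):

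- p = 0.17: √(2·0.17·0.83/65) = 6.6 points
- p = 0.57: √(2·0.57·0.43/65) = 8.7 points

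Exact binomial and hypergeometric enumeration gives a difference of at least 10 points with probability 10–13% at 17% use and 21–25% at 30–57% use. For at least 15 points the range is 3–11%.

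**With the planned dose stratification.** Simulation of 130 participants. Assumptions: blocks of 4; classes independent; users 50% low, 40% half and 10% maximum dose. The stratum was set in two ways: any class at 50% or more, or both classes at 50% or more. Share of trials with an arm difference of at least 10 points:

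| ACEi/ARB use / MRA use | Imbalance in ACEi/ARB use | Imbalance in MRA use |
|---|---|---|
| 36% / 17% | 16–23% | 10–12% |
| 84% / 57% | 10–12% | 23–24% |

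For MRA use these are close to the unstratified figures, so the dose cut does almost nothing for class balance. Adding ACEi/ARB use and MRA use as strata brings both columns to about 0%. A rerun with MRA use as the only added factor brings the MRA column to about 0% but leaves ACEi/ARB imbalance at about 11–23%.

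**What an imbalance could do to the estimate.** The article gives no effect of MRA status on response. If it were 30 points (assumption), a 10-point imbalance would move the estimated difference by 0.10 × 30 = 3 points, a tenth of the planned 30. If it were 10 points, the shift would be 1 point. The standard error of the difference at 65 per arm is √((0.25 + 0.16)/65) = 7.9 points, so 3 points is about 0.4 standard errors.

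**Secondary point: Table 3 against a 50% cut.** Listed half-maximum dose divided by listed maximum:

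| Drug | Half-maximum | Maximum | Fraction |
|---|---|---|---|
| Enalapril | 5 mg | 10 / 20 / 40 mg | 50% / 25% / 12.5% |
| Lisinopril | 5 mg | 20 / 40 mg | 25% / 12.5% |
| Lisinopril | 10 mg | 20 / 40 mg | 50% / 25% |
| Perindopril erbumine | 4 mg | 8 / 16 mg | 50% / 25% |
| Candesartan | 8 mg | 32 mg | 25% |
| Candesartan | 16 mg | 32 mg | 50% |

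The other ten listed products are consistent with a 50% cut.

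**Secondary point: two classes, one percentage.** With levels of 0, 25, 50 and 100% per class, and maximum on both excluded, there are 15 profiles. Under three readings (any class at 50% or more, all classes, mean), 8 of the 15 change stratum. Each has one class at 50% or more and the other absent or low.

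**The case against.** The strongest reply is that this is a condensed article. The reference dose and the rule for combining two classes are operational details that may stand in the full protocol, and the Randomisation section does not cite Table 3. That stands, and it is why the Table 3 ambiguity is secondary and conditional. It does not rescue the stated purpose: no definition of the reference dose makes a two-level dose cut balance drug class.

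A second reply is that a 10–25% chance of a 10-point imbalance is ordinary chance variation, already covered by the 5% error rate. That is correct for validity. The point is only that the text promises equality that the design does not deliver.

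A reader might also infer that many participants have no determinable stratum. The documents do not support this:

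- Someone on one class at half maximum most naturally has one baseline dose, at 50% or more. On that reading only two-class users at discordant levels are unclear. If half of users are at 50% or more (assumption, classes independent), that is 0.36 × 0.17 × 0.5 ≈ 3% (about 4 of 130) at the CKD 4/5 rates and 0.84 × 0.57 × 0.5 ≈ 24% at the non-CKD rates.
- On the widest reading the share runs from about 5% to 52% (about 7 to 67 of 130), depending wholly on an assumed fraction of users at 50% or more. The article's audit gives only the share at maximum dose ("only 3% of all patients with left ventricular systolic dysfunction were on maximum-dose ACEi/ARB, and only 2% were on maximum-dose MRA"), which does not settle that fraction.
- At the CKD 4/5 rates, between 100 − (36 + 17) = 47% and 100 − 36 = 64% would take no RAASi and fall plainly in the lower stratum.

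The extra visit for untreated participants follows from baseline status in both arms alike. It shows that the lower stratum is mixed; it is not a defect in itself.

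**Conclusion.** The claim that stratification ensures equal proportions of RAASi therapies is not correct as written. The factor balances one dose split and leaves MRA use, ACEi/ARB use and no-versus-some therapy to chance. For MRA use, an imbalance of at least 10 points remains in roughly 10–25% of trials of 130. That range rests on the article's prescribing rates, which come from a hospital-admission cohort and not from trial participants, and on an assumed dose mix and block size.

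The Table 3 ambiguity is real for certain doses of four drugs if Table 3 is the reference, and for some participants at different levels in two classes. Its frequency is unknown.

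A reader might go further and infer that the randomisation or the test is compromised. Neither follows. The stratum is set before allocation, so inconsistent assignment does not bias the comparison, and the χ² test does not use it. Nor is an imbalance beyond repair, since baseline class and dose can be used as covariates. The loss is in balance and precision, and in a stated property that the design lacks.

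**What to change.** 1. **If recruitment has not started:** add baseline MRA use (yes/no) as a second stratification factor. The cost is a revised list and four strata instead of two, which 130 participants can support, although at 17% use only about 22 (130 × 0.17) would be MRA users. This secures MRA balance but not ACEi/ARB balance, so the stated purpose should name only the factors actually stratified.
2. **If recruitment has started:** keep the list and adjust the primary analysis for baseline RAASi class and dose, fixed before unblinding. The plan reports a difference in proportions, so the adjusted result should also be given on that scale. The cost is a short change to the analysis text.
3. **If neither is wanted:** limit the stated purpose to balance of the dose strata. The cost is one sentence.
4. **In every case:** name the reference dose behind the 50% cut, reconcile it with Table 3 so that each drug and dose falls in one stratum, and state which class decides when two classes differ or one is absent. If the full protocol already does this, a cross-reference is enough.
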